## 3. Procedures

### 3.1. Phase 1

In this phase, the exercise facilitator (EF) will be set up in the dialysis center. He/she will be an experienced physiotherapist and/or qualified exercise specialist who will be active in the dialysis centers for a specified number of hours per day to counsel patients concerning their worries and answer questions concerning physical activity. The EF will be properly trained by the members of the Rehabilitation Medicine Unit at the University Hospital of Ferrara on the management of frail patients by having experience with severely disabled patients with different conditions before the beginning of the study.

Stakeholder involvement: The EF, in collaboration with the team members, will prepare the informative material for the project. Team members will arrange meetings with unit personnel and coordinators of patient groups to introduce the EF figure, to explain the aims of the project and to address doubts and questions.

After the baseline outcome assessment, the EF will propose one of the four interventions to the patients by means of a specifically designed brochure, which is explained in the following section.

Qualitative outcomes will be employed in the first phase (Table 1). The rate of patients providing consent compared to the number of eligible patients, as well as the rate of patients choosing each of the training options proposed, will be calculated to determine patients’ willingness to exercise and their preferences about training. The impact of the patients’ characteristics and other variables on the choice of the program will also be investigated.

### 3.2. Phase 2

The EF will ask each enrolled patient to select an intervention and thus enter into one of the following arms.

Unstructured physical activity (U-PA)

According to each patient’s baseline physical activity level previously measured, the EF will advise patients to start or increase their spontaneous activity by counseling them on total exercise time, mode, intensity and frequency as suggested by the guidelines [27,28] (Table 2). A log-book and a wearable physical activity monitor will be provided to each patient. The instruments have to be returned in the subsequent controls, to encourage adherence and objectively measure the exercise activities.

Structured home-based low-intensity exercise (S-HB-LI)

According to each patient’s baseline physical activity level, a semipersonalized walking program will be provided. This program, derived from previous experience with ESKD patients [13,29] was also successfully tested in other fragile populations such as stroke survivors or multiple sclerosis patients [30,31,32]. The training program will be performed at home at a prescribed speed and it includes a 10-min session/day of intermittent walking (1- or 2-min work and 1-min seated rest). The speed which is converted into a walking cadence is increased weekly and it is controlled at home with the aid of a metronome (Table 2). Patients will be provided with a daily log containing the detailed exercise prescription and free lines to provide feedback on training execution and any possible related symptoms.

Structured supervised low-intensity exercise (S-SU-LI)

Patients will meet at a specified location (room or corridor) into the dialysis unit for the exercise program in groups of a maximum of four subjects. The thirty-minute training session will be scheduled on a 2- or 3-time/week pattern, and they will be performed immediately before or after the dialysis treatment or according to patients’ preferences and considering the postdialysis fatigue that affects this population [33].

Each session will include low-intensity walking exercises (similar to those for the structured home-based training) and resistance and power exercises with elastic bands and ankle/wrist weights. Each session will begin and end with a warm-up and cool-down period of stretching, respectively. The total duration of the session will be approximately 30 min. The training intensity will be set according to the patient’s baseline capacity and it will be weekly increase. The rate of perceived exertion will be always collected (Table 2).

Physical performance assessment only (PPA)

Patients choosing this option will not begin any exercise program, but they will perform the outcome measures session only. A switch to another treatment, periodically proposed by the EF, will be always possible.

Study design is presented in Figure 1.

### 3.3. Discontinuing the Intervention

Patients who chose one of the three training options will be interviewed weekly by the EF to monitor their adherence to the program. Additionally, daily logs will be reviewed when possible. In general, all the intercurrent pathologies affecting the patients in training will be noted.

As this is a nonrandomized study in which patients will choose their preferred option, a switch within the different training modalities will always be possible. However, team members will try to motivate patients to complete the chosen 3-month program.

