### 3.6. Phase 2 Outcomes

First, the feasibility and safety of the exercise programs will be assessed in terms of adverse events, falls and intercurrent problems. In addition, the adherence of each patient to the selected training option will be determined by analyzing the number of sessions completed, the total minutes of training and the percentage of patients that reached the amount of physical activity indicated by the guidelines.

Quantitative outcomes will be collected before the beginning of the training program, at the end of the training program (three months) and at the six-month follow-up.

The primary outcome will be exercise capacity, assessed through the 6-min walking test. Subjects will be instructed to walk with their habitual walking device as far as possible in 6 min. The test will be performed on a 22-m walkway. The patients will have the possibility of slow down and rest if necessary. The total distance walked, the pain-free walking distance and the perceived exertion at the end of the test (Borg Scale 1–10) will be recorded [34] (Table 1).

Secondary outcomes will include the following:Gait speed, assessed through the 10-m walking test.Lower limb strength, evaluated with the 5-time sit-to-stand test.Health-related QoL, measured by the Italian version of the Short Form Health Survey (SF-36).Fear of falling, assessed through the Short Falls Efficacy Scale.Estimated functional capacity, measured by the Duke Activity Status Index.Depression, evaluated by the Beck Depression Inventory—II and the demoralization scale.Heart rate, oxygen saturation and blood pressureLaboratory outcomes: Serum creatinine levels, estimated glomerular filtration rate, Kt/v, glycaemia, total cholesterol and a full blood count will also be determined.Long-term outcomes: Other clinical outcomes, such as mortality and all-cause hospitalization, will be recorded at 3, 6, 12 and 24 months from the end of the exercise program.

A detailed description of secondary outcomes is available in the Supplementary Material 1.

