### 3.8. Sample Size

To the best of our knowledge, this is the first trial of this type exploring patient preferences about programs and comparing the outcomes for these programs. Therefore, a power calculation hypothesizing a better effect of one program compared to another could not be performed; in addition, the investigators do not assign the interventions, and they do not know a priori how many patients will select each training option.

Otherwise, we aim to recruit a sufficient number of participants to address the study’s implementation objectives. The Nephrology Unit at the University Hospital of Ferrara manages approximately 140 patients on dialysis. The entrance of new patients into dialysis service will be checked every 3 months. We will try to propose the programs to all eligible patients and hypothesize a 50% rate of acceptance, which might be progressively increased by word of mouth among patients.

According to a power calculation based on a theoretical responder rate of 50% and considering a margin of error equal to 5% and a confidence level of 90%, a total of 88 patients will be required to make the first qualitative phase of the study representative of the population.

To optimize recruitment, all members of the Nephrology Unit of the hospital will be informed about the trial during team meetings. Information on the study procedures will also be given to the CKD and ESKD support groups, which will share the study information through their newsletters and website.

The EF will be available daily in the dialysis room to encourage patient participation. Informative material will also be available in the Nephrology Unit wards.

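### Intercurrent illness is to be noted for patients in training only, so the assessment-only arm would not give an equally ascertained background rate for safety

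*Protocol article*

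**What the plan says.** Section 3.6 opens the Phase 2 outcomes with feasibility and safety: the "safety of the exercise programs will be assessed in terms of adverse events, falls and intercurrent problems".

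Section 3.3 describes follow-up during the programme. "Patients who chose one of the three training options will be interviewed weekly by the EF to monitor their adherence to the program". It adds: "Additionally, daily logs will be reviewed when possible". The paragraph closes by stating that "all the intercurrent pathologies affecting the patients in training will be noted".

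For the PPA arm, Section 3.2 says: "Patients choosing this option will not begin any exercise program, but they will perform the outcome measures session only". The only other facilitator contact described for that arm is the offer to change: "A switch to another treatment, periodically proposed by the EF, will be always possible".

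Table 2 points in a different direction. Its Monitoring row has four entries for four columns, and the last, a daily log, appears to belong to PPA. In Table 1 the safety row is not restricted to any arm and carries one mark, at 3 months.

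**The concern.** Falls and intercurrent illness happen to dialysis patients whether or not they exercise. The Introduction itself links impaired physical performance to falls. A count of such events in exercising patients is hard to interpret without some idea of how often they occur in similar patients who do not exercise. The trial has a non-exercising arm that could give that context, but one component of the safety outcome is recorded under a rule that names only patients in training.

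At stake is how the safety result will be read. Section 5 expects the study to inform on the safety of the programmes, and readers will set the four arms side by side whether or not a test is planned. If events are looked for harder in three arms than in the fourth, those three will tend to look worse for that reason alone. Baseline adjustment cannot repair a difference in ascertainment. Switching adds to the problem: a PPA patient who starts a programme moves into closer follow-up, so the recorded rate may rise through recording alone.

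**Working it through.** The protocol states no adverse event rate, safety sample size or capture rate, so there is no figure of its own to reproduce. The check compares what is described for each arm over the 3 months.

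| Source of event information | Three training arms | PPA |
|---|---|---|
| Weekly facilitator interview (3.3) | Yes; stated purpose is adherence | Not described |
| Noting of intercurrent illness (3.3) | Yes | Not described; the sentence covers patients in training |
| Outcome sessions (3.6) | Baseline, 3 and 6 months | Baseline, 3 and 6 months |
| Monitoring (Table 2) | Log and activity monitor; log; facilitator | Daily log, content not described |
| Facilitator offer to switch (3.2, 3.3) | Switching possible | Periodic offer; no event enquiry described |
| Harms procedure (3.4) | Evaluation of fitness to continue the programme | Does not fit an arm without a programme |
| Safety row (Table 1) | 3 months, not arm-specific | 3 months, not arm-specific |
| Hospitalization and mortality (3.6) | All arms, timed from the end of the programme | Same |

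**Step 1. Is the rule unequal as written?** Yes, for intercurrent illness: the sentence in Section 3.3 covers patients in training. For falls and other adverse events the inequality is probable but inferred, because no passage says how they are elicited in any arm.

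**Step 2. Do the other sources close the gap?** Only in part.
- The one log whose content the protocol describes, in the home-based programme, carries the exercise prescription and feedback on training and related symptoms. That does not fit a patient with no programme.
- A PPA log also sits badly with the statement that these patients "they will perform the outcome measures session only".
- Hospitalization and mortality are timed from the end of the programme, so they are not stated to cover the training window. They also miss falls and minor illness.

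**Step 3. What could unequal capture do?** Observed proportion = true proportion × capture probability. With equal true proportions, the observed ratio of training to PPA is 1/r, where r is PPA capture divided by training capture. All values of r below are assumptions.
- r = 1: ratio 1.0
- r = 0.8: ratio 1/0.8 = 1.25
- r = 0.5: ratio 1/0.5 = 2.0
- r = 1/3: ratio 3.0

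In absolute terms, assume a true 3-month proportion of 30% and 90% capture in training, so 0.30 × 0.90 = 27% observed. PPA capture of 60%, 45% or 30% gives 18%, 13.5% or 9% observed. The spurious differences are 9, 13.5 and 18 percentage points. With 90% capture in both, the difference is zero. These figures show the direction and the mechanism; they do not estimate the bias in this trial.

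**The case against.** The strongest reply has four parts.

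1. **Purpose of the interview.** Its stated purpose is adherence, and PPA patients have no programme to adhere to. A reader might infer that adverse events are collected by weekly interview in three arms and not in the fourth. The protocol does not say that. It follows that 12 weekly contacts against one 3-month visit is not a valid measure of the imbalance. It would count adherence interviews as event enquiries and ignore the PPA log and the facilitator's repeat offers. This part stands. The sentence on intercurrent illness does not depend on it.

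2. **Some capture in PPA.** The Table 2 log, the unrestricted safety row in Table 1, and hospitalization and mortality all provide something. A reader might infer that PPA yields no background information at all; that goes too far. What is missing is a background rate ascertained in the same way.

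3. **No planned safety contrast.** Section 3.6 treats safety as a property of the programmes. The between-group analysis in Section 3.10 covers the primary and secondary outcomes, and falls and adverse events are in neither list. So no planned test is shown to be biased. The arms will still be read side by side.

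4. **Self-selection and condensed reporting.** Patients choose their arm and Section 4.2 expects fitness to drive the choice, so equal recording would not make PPA an unconfounded control. That stands and limits what the fix can achieve. An article may also leave event elicitation to the full protocol. That excuses silence, but Section 3.3 states a rule that differs by arm.

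**Conclusion.** The point holds in a limited form. As written, intercurrent illness is noted for patients in training and not for PPA, and falls and other adverse events would probably follow the same pattern. The trial would then lack an equally ascertained background rate, and a side-by-side reading would tend to count against the programmes. The PPA text in Section 3.2 and the PPA entry in Table 2 also do not agree.

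The size is unknown. The 1.0 to 3.0 range for the observed ratio rests wholly on assumed relative capture between 1 and one third and on equal true rates. The direction rests on PPA capture being the less active, which the described procedures suggest but do not prove. Capture may also differ among the training arms, since Table 2 has the facilitator monitor the supervised arm while the other two rely on logs.

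This is an avoidable weakness in a descriptive safety outcome. It does not invalidate the trial's feasibility aims, and the protocol does not support saying that the programmes' safety cannot be assessed at all.

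**What to change.** Change Section 3.3 so that falls, adverse events and intercurrent illness over the 3 months are recorded in the same way for every enrolled patient in all four arms: same items, same interval, same recorder. Dialysis-unit records are the preferred source because they leave PPA contact unchanged. Weekly facilitator questions to PPA patients would also equalize capture, and "The EF will be available daily in the dialysis room", but they would add facilitator contact to an arm defined by assessment only, in a trial of the facilitator's influence.

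Reconcile Section 3.2 with the PPA entry in Table 2. If PPA patients do keep a log, state what it records.

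Report event rates per patient-time by arm with 95% intervals, as description, and say that the arms are self-selected and that PPA is not an unconfounded control. If equal recording is not adopted, report safety for the training arms without contrast to PPA.

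The cost is a small amount of chart extraction for PPA patients. Unit records may miss minor events that nobody reports to the unit. To keep the comparison even, events known only through the facilitator's weekly contact should be shown separately.

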### 3.4. Harms

This trial, which uses well-established and safe exercise programs [13,29,30,31,32], in combination with rigorous handling of potential harms per local hospital policy, expects to minimize all the potential risks. If an undesired effect of training or a concomitant or intercurrent disease occurs, patients will be thoroughly evaluated by the team members to determine their eligibility for continuing the program, which will otherwise be stopped. Any potential harm will be treated according to the local University Hospital policy that also encompasses insurance coverage.

### 3.5. Concomitant Care and Recommendations

During the training period, patients will be asked to maintain their habitual lifestyle. Concomitant treatments (e.g., physiotherapy sessions) will be allowed, but an appropriate analysis will be carried out when analyzing the outcomes. Finally, patients will be asked to wear the same shoes and orthosis during all the testing and training sessions.

At the end of the 3-month training period, patients will be suggested to maintain a sufficient level of physical activity. To determine the amount of exercise performed during the follow-up period, patients will be asked to compile a daily log or to wear a fitness tracker.

### 3.6. Phase 2 Outcomes

First, the feasibility and safety of the exercise programs will be assessed in terms of adverse events, falls and intercurrent problems. In addition, the adherence of each patient to the selected training option will be determined by analyzing the number of sessions completed, the total minutes of training and the percentage of patients that reached the amount of physical activity indicated by the guidelines.

Quantitative outcomes will be collected before the beginning of the training program, at the end of the training program (three months) and at the six-month follow-up.

The primary outcome will be exercise capacity, assessed through the 6-min walking test. Subjects will be instructed to walk with their habitual walking device as far as possible in 6 min. The test will be performed on a 22-m walkway. The patients will have the possibility of slow down and rest if necessary. The total distance walked, the pain-free walking distance and the perceived exertion at the end of the test (Borg Scale 1–10) will be recorded [34] (Table 1).

Secondary outcomes will include the following:Gait speed, assessed through the 10-m walking test.Lower limb strength, evaluated with the 5-time sit-to-stand test.Health-related QoL, measured by the Italian version of the Short Form Health Survey (SF-36).Fear of falling, assessed through the Short Falls Efficacy Scale.Estimated functional capacity, measured by the Duke Activity Status Index.Depression, evaluated by the Beck Depression Inventory—II and the demoralization scale.Heart rate, oxygen saturation and blood pressureLaboratory outcomes: Serum creatinine levels, estimated glomerular filtration rate, Kt/v, glycaemia, total cholesterol and a full blood count will also be determined.Long-term outcomes: Other clinical outcomes, such as mortality and all-cause hospitalization, will be recorded at 3, 6, 12 and 24 months from the end of the exercise program.

A detailed description of secondary outcomes is available in the Supplementary Material 1.

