To fulfill these requirements in the ESKD population, several physical, psychological and environmental barriers that are still present need to be overcome. First, the identification of sustainable programs with good adherence is a priority because of these barriers [18,19,20]. Moreover, a proactive dialysis staff attitude is another crucial issue [21,22]; unfortunately, physical activity and exercise management are not routinely addressed in the care of these patients [2]. Although motivators to exercise have been reported in other diseases [23], nurse-led disease management programs in patients on dialysis have been tested [24,25] but not for promoting physical activity.

This pragmatic trial aims to test the impact of the regular presence of an exercise facilitator in a dialysis center to promote physical activity in the ESKD population. The efficacy will be verified in terms of applicability and feasibility, and the preferred and most effective exercise pathways for the patients will be identified. Secondarily, the study aims to carry out exploratory analyses to evaluate the impact of different exercise interventions on the functional and clinical parameters of the patients.

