## 2. Experimental Design and Methods

### 2.1. Trial Design

This protocol is reported following the Standard Protocol Items: Recommendations for Interventional Trials (SPIRIT) guidelines [26]. The study is a pragmatic feasibility nonrandomized implementation trial that also includes a qualitative research study.

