**Outcomes**					
*Phase 1*					
% Patients responders/eligible		X			
Physical and emotional status		X			
Exercise program choices		X			
Factors related to choices		X			
*Phase 2*					
Safety (adverse events, interruptions)			X		
Adherence (% sessions completed)			X		
6MWT (primary outcome)		X	X	X	
Gait speed, lower limbs strength, quality of life, depression, estimated capacity, fear of falling (secondary)		X	X	X	
Biochemical/laboratory markers		X	X	X	
Hospitalizations and mortality				X	X

Abbreviations: U-PA-I: unstructured physical activity increase; S-HB-LI: structured home-based low-intensity; S-SU-LI: structured supervised low-intensity; PPA: physical performance assessment; 6MWT: 6-min walk test.

**Table 2 mps-03-00083-t002:** The different interventions proposed to the patients by the exercise facilitator.

Program	U-PA-I			S-HB-LI			S-SU-LI			PPA Performance Assessment
	Unstructured Physical Activity Increase			Structured Home-Based Low Intensity			Structured Supervised Low Intensity			
*Setting*	Home			Home			Dialysis Center			-
*Frequency*	Daily			Daily			2- or 3-Time a Week			
*Baseline 6MWD (m)*	<200	201–400	>400	<200	201–400	>400	< 200	201–400	>400	-
*Program features*	Walking (mins) Intensity: moderate [27,28]			Walking: rest (min) × reps Speed (steps/min)			Walking * + strength leg extension/leg curl/shoulder abduction (reps × series − load)			
*Week 1*	5	10	15	1:1 × 6 − 60	1:1 × 8 − 60	1:1 × 8 − 72	3 × 2 – 0.5 kg	3 × 3 − 1 kg	3 × 3 – 1.5 kg	-
*2*	5	10	15	1:1 × 6 − 63	1:1 × 8 − 63	1:1 × 8 − 76	3 × 2 – 0.5 kg	3 × 3 − 1 kg	3 × 3 – 1.5 kg	
*3*	10	15	20	1:1 × 8 − 63	1:1 × 8 − 66	1:1 × 8 − 80	4 × 2 − 1 kg	4 × 3 − 1 kg	4 × 3 – 1.5 kg	
*4*	10	15	20	1:1 × 8 − 66	1:1 × 8 − 69	1:1 × 8 − 84	4 × 2 − 1 kg	4 × 3 − 1 kg	4 × 3 – 1.5 kg	
*5*	15	15	20	1:1 × 8 − 66	1:1 × 8 − 72	1:1 × 8 − 88	3 × 3 − 1 kg	4 × 3 – 1.5 kg	4 × 3 − 2 kg	
*6*	15	20	20	1:1 × 8 − 69	1:1 × 8 − 72	1:1 × 8 − 92	3 × 3 − 1 kg	4 × 3 – 1.5 kg	4 × 3 − 2 kg	
*7*	15	20	25	1:1 × 8 − 69	1:1 × 8 − 76	2:1 × 4 − 72	4 × 3 − 1 kg	4 × 4 – 1.5 kg	4 × 4 − 2 kg	
*8*	20	20	25	1:1 × 8 − 72	1:1 × 8 − 76	2:1 × 4 − 76	4 × 3 − 1 kg	4 × 4 – 1.5 kg	4 × 4 − 2 kg	
*9*	20	20	25	1:1 × 8 − 72	1:1 × 8 − 80	2:1 × 4 − 80	4 × 3 – 1.5 kg	4 × 4 − 2 kg	4 × 4 – 2.5 kg	
*10*	20	25	25	1:1 × 8 − 76	1:1 × 8 − 80	2:1 × 4 − 84	4 × 3 – 1.5 kg	4 × 4 − 2 kg	4 × 4 – 2.5 kg	
*11*	20	25	30	1:1 × 8 − 76	1:1 × 8 − 84	2:1 × 4 − 88	4 × 4 – 1.5 kg	5 × 4 − 2 kg	5 × 4 − 3 kg	

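### The 6-min walk test is the only outcome labelled primary, yet functional effects are called exploratory and the sample size rests on uptake alone; the text does not reconcile these

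*Protocol article*

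**What the plan says.** **Design and aim.** Section 2.1: "The study is a pragmatic feasibility nonrandomized implementation trial that also includes a qualitative research study". On the aim, the Introduction says: "The efficacy will be verified in terms of applicability and feasibility". The same sentence adds that "the preferred and most effective exercise pathways for the patients will be identified". The next sentence reads: "Secondarily, the study aims to carry out exploratory analyses to evaluate the impact of different exercise interventions on the functional and clinical parameters".

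**Outcomes.** Section 3.6 begins Phase 2 with feasibility, safety and adherence, and then turns to the quantitative measures: "The primary outcome will be exercise capacity, assessed through the 6-min walking test". Table 1 marks the 6-min walk test (6MWT) as primary in its Phase 2 block. The ratio of responders to eligible patients is in the Phase 1 block and has no rank.

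**Size.** Section 3.8 says that "a power calculation hypothesizing a better effect of one program compared to another could not be performed", and that the number of patients choosing each option is not known in advance. It then requires 88 patients, from a 50% responder rate, a 5% margin of error and 90% confidence, for the first phase.

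**Analysis.** Section 3.10 compares primary and secondary outcomes by two-way repeated-measures analysis of variance, adds within-group paired tests, and sets significance at 0.05. An adjusted analysis follows only if baseline characteristics differ significantly between groups. A post hoc power analysis is planned.

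**The concern.** A primary outcome is normally the one that the trial is sized for and draws its main conclusion from. Here the label goes to a functional measure, a kind of measure that the Introduction treats as exploratory. The one quantity with a sample size calculation, the uptake rate, has no label.

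The risk lies in interpretation. A non-significant walk-test comparison could be taken to show that the programs do not differ, or that the exercise facilitator has no effect. A significant one could be taken as confirmed superiority of one program. The comparison was not sized for either conclusion, and patients choose their own arm. Section 4.2 itself expects fitter patients to prefer certain programs, so fitness, which is close to the outcome, may drive the choice.

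**Working it through.** **Step 1. Does the stated size contain anything about the walk test?**

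Inputs from Section 3.8: p = 0.50, margin e = 0.05, 90% confidence (z = 1.645, two-sided), about 140 patients in the unit.

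- Without finite-population correction: n0 = z²p(1 − p)/e² = 1.645² × 0.25/0.0025 = 270.6.
- With correction at N = 140: n = n0N/(n0 + N − 1) = 270.6 × 140/409.6 = 92.5, so 93.
- The stated 88 is not reproduced at N = 140. It comes back at N of about 130 (88.03), a figure that the article does not give.

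In each variant the only inputs are the uptake proportion, its margin, the confidence level and the population size. No walk-test difference, standard deviation or power enters. The size rests on uptake alone.

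**Step 2. What precision does 88 give for uptake?**

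Margin at 90% confidence: 1.645 × √(0.25/88) = 8.8 percentage points. With the correction √((140 − 88)/139) = 0.61 it is 5.4 points. This is close to the stated 5 points but does not reach it.

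**Step 3. What could that size show on the walk test? (illustration)**

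Assumptions that are not in the article: four equal arms, one pairwise comparison of independent groups by t-test, two-sided 0.05, no dropout, no multiplicity or baseline adjustment. Here d is the difference in standard deviations.

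| Enrolled | Per arm | d for 80% power | Power at d = 0.5 |
|---|---|---|---|
| 88 (stated number, if it means enrolled) | 88/4 = 22 | 0.86 | 37% |
| 70 (50% of 140) | 70/4 = 17.5 | 0.98 | 30% |

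The normal approximation, d = (1.96 + 0.84) × √(2/n), gives slightly lower values: 0.84 at n = 22 and 0.95 at n = 17.5. By the same approximation, d = 0.5 would need 63 per arm. Unequal arms do worse: 10 against 30 patients needs d = 2.80 × √(1/10 + 1/30) = 1.02.

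The article gives no standard deviation for the walk test. If the SD of change were 50 to 80 m (assumption), 0.86 SD is 43 to 69 m and 0.98 SD is 49 to 78 m.

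**Step 4. The statements side by side**

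| Place | Standing of the walk test or of functional effects |
|---|---|
| Introduction | Secondary aim, exploratory |
| Section 3.6 and Table 1 | Primary, and the only outcome so named |
| Section 3.8 | Comparison of programs not powered |
| Section 3.10 | Compared between arms, 0.05 threshold |

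No sentence says how an exploratory effect comes to be the primary outcome, or that the label is limited to one phase.

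**The case against.** The strongest reply concerns scope. The label stands under the heading for Phase 2 outcomes, after feasibility, safety and adherence, and Table 1 keeps the Phase 1 outcomes in a separate block. A two-phase hierarchy, in which the walk test leads only the quantitative Phase 2 measures, is a natural reading. It cannot be ruled out, and the fix adopts it. What remains is that the article never states it and names no lead outcome for Phase 1.

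Second, the main-aim sentence also looks for the most effective pathways, so effectiveness is not wholly outside the main aim. That softens the contrast. It does not remove it, because the next sentence makes the evaluation of functional effects exploratory.

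Third, the weaknesses are disclosed. Section 3.8 admits the missing power calculation, Section 4.2 concedes selection bias and a possibly small sample, and Section 3.10 plans an adjusted model. This stands, and it would be unfair to say that confounding is ignored. But the adjustment depends on a significant baseline difference, neither it nor the post hoc power analysis supplies prospective power, and none of these passages changes the rank of the outcome.

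Fourth, the detectable differences in the working come from an unadjusted pairwise t-test, not the planned analysis of variance. That is correct. They indicate scale only, and the point does not depend on them, since Section 3.8 already says that the comparison is not powered.

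**Conclusion.** The point holds as an unreconciled inconsistency: the same functional measure is primary in Section 3.6 and Table 1 and falls under an exploratory aim in the Introduction, in a trial sized on uptake only. It should be corrected, because the label decides which result readers take as the trial's answer.

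A reader might infer three stronger things that the article does not support:

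- *That the outcome hierarchy flatly contradicts the aim and ranks feasibility below the walk test.* No passage ranks feasibility lower, the label may apply to Phase 2 only, and the main aim also mentions effectiveness.
- *That uptake, by contrast, is answered with the stated precision.* On the article's own figures, 88 of about 140 gives about 5.4 points at 90% confidence, and 5 points needs about 93. It is also unclear whether 88 counts patients approached or patients enrolled.
- *That the walk test must be replaced as the primary outcome.* The trial is registered and ethics-approved, and the registry record is not at hand. Stating the scope and status of the label is enough.

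The power figures (about 0.86 SD at 22 per arm, about 0.98 SD at 17.5 per arm) assume equal arms and one pairwise t-test. Arms that patients choose themselves may well be unequal, which would make the figures worse.

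**What to change.** Amend Sections 3.6 and 3.10 and Table 1 together:

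1. Name the rate of consenting to eligible patients, with its confidence interval, as the lead (Phase 1) outcome, and say that the sample size was computed for it.
2. State that the 6MWT is the leading functional outcome of Phase 2 only, and that it is exploratory and unpowered.
3. In Section 3.10, report the 6MWT as baseline-adjusted differences between arms with 95% intervals, whether or not baseline tests are significant, and without a claim of confirmatory significance.

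The cost is wording. Recruitment, assessments and data collection do not change. The registry entry should be checked against the new text and updated if it differs. The small downside is that a favourable walk-test result can no longer be presented as confirmatory.
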